**OBJECTIVES, DESIGN, AND HYPOTHESES**

The purpose of this study is to examine the efficacy, feasibility, and acceptability of videoconferencing-delivered CBT for anxiety disorders in LGBTQ+ adults. A CONSORT-R compliant, two-group, randomised control feasibility trial (RCT) will examine the research questions. The hypotheses for this study are below:

1. Videoconferencing-delivered, standard CBT will result in significant reductions in symptoms with a large between-group and within-group effect size at post-treatment and three-month follow-up.
2. Videoconferencing-delivered, LGBTQ-adapted CBT will result in a similar degree of symptom reduction when compared to standard CBT.
3. Videoconferencing-delivered standard CBT and LGBTQ-adapted CBT will be feasible to deliver to LGBTQ+ adults with diagnosed anxiety, as assessed by at least 80% treatment fidelity (Borrelli et al., 2005), at least 80% retention following the waitlist period (Fernandez et al., 2015).
4. Videoconferencing-delivered CBT will be acceptable to LGBTQ+ adults with diagnosed anxiety disorders, as assessed in qualitative semi-structured exit interviews and by at least 70% treatment retention and questionnaire completion at follow-up (Fernandez et al., 2015).

The study’s design has two groups:

**Group 1 (*n* = 26): Immediate treatment group.** Group 1 will immediately receive standard, unadapted CBT delivered via videoconferencing. This treatment will be delivered via Zoom. Participants in Group 1 will receive one 50-minute session per week for eight weeks.

**Group 2 (*n* = 26) Waitlist control group.** Group 2 will commence the treatment after a waitlist period of nine weeks, and will recomplete screening measures and their diagnostic interview. Group 2 will receive a similar CBT treatment delivered via Zoom, but this treatment has been tailored to account for the unique challenges experienced by LGBTQ+ people (Pachankis, 2014). LGBTQ-adapted treatment has been shown to be efficacious in previous trials (Pachankis et al., 2015; Pachankis et al., 2020).

A waitlist control was chosen given no studies have currently investigated standard CBT for internalising disorders in LGBTQ+ individuals. As such this study is designed as a feasibility study, phase 1 clinical trial.

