**Summary**

| **Overall project title:** | Remote Cognitive Behavioural Therapy for LGBTQ+ People with Anxiety Disorders: An Exploratory Trial |
| --- | --- |
| **Protocol version** | 2.3 |
| **Objectives** | **Primary**  The primary objective of this program of research is to understand how efficacious cognitive behavioural therapy (CBT) is when delivered via videoconferencing for anxiety disorders in LGBTQ+ adults.  **Secondary**  The secondary objectives of this project are: 1) to benchmark the efficacy of adapted CBT compared to standard CBT for LGBTQ+ adults, when both are delivered via video-conferencing; 2) to understand the feasibility of delivering CBT to LGBTQ+ adults via video-conferencing; and 3) understand the perspectives of LGBTQ+ participants on the content, delivery format, and acceptability of CBT delivered via telehealth for anxiety disorders. |
| **Study design** | A randomized controlled trial (RCT) compliant with CONSORT-R guidelines, comparing an immediate treatment group with a waitlist control group, with a nested qualitative study to examine acceptability of the treatment. |
| **Planned sample size** | A total sample of 52 participants, with 26 participants in each group. Qualitative interviews will use 8 - 10 participants from each intervention group, with a total of 16 - 20 included participants in qualitative evaluation interviews. |

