| **Statistical considerations** | **Sample size calculation**  The sample size calculator developed by Faul et al. (2007) was used to calculate a total sample size of 52 participants, in samples of 26 for each group, to detect a large effect (*d* = .80) with 80% power. Previous research has indicated that CBT has a large effect size for anxiety disorders (Cuijpers et al., 2013). To detect clinically significant differences in participant diagnostic status, 42 participants will need to be recruited, in samples of 21 in each group, using the ClinCalc LLC (2024) sample size calculation tool.  A total of 16 – 20 participants will be selected for inclusion to the qualitative study, with eight to ten participants each from each intervention group. Braun and Clarke (2013) recommend that 10 to 20 participants are typically sufficient to identify themes, although, previous researchers have suggested that fewer participants may be needed if the sample holds more information power. This sample size is consistent with other sample sizes in this area of research (Jackson et al., 2022; Pachankis et al., 2020). Participants will be selected based on a representative matrix to achieve a maximally diverse qualitative sample, consistent with other qualitative studies (Christensen et al., 2023).  **Analysis plan**  To ensure analyses manage missing data conservatively, intent-to-treat principles and mixed-linear models will be used for quantitative analyses. Mixed-models are used to analyse longitudinal clinical trial data robustly. Using an appropriate covariance structure and maximum likelihood estimation will provide unbiased estimates in the event of missing data, assuming that data is missing at random. Qualitative data will be analysed using framework analysis (Ritchie & Spencer, 1994). |
| **Study duration** | 5 years |

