**PARTICIPANT NUMBERS & POWER**

Using G*Power, it was determined that 52 participants would be needed to detect a large, post-treatment, between-group effect size with alpha set to 0.05 and 80% power (Faul et al., 2007). This is because previous meta-analyses have detected large effect sizes for the effect of CBT on anxiety (Cuijpers et al., 2013). Previous preliminary randomised control trials of CBT for LGBTQ+ adults with both internalising and externalising disorders have recruited samples of similar sizes (Pachankis et al., 2015; Pachankis et al., 2020).

Power was also calculated to detect clinically meaningful changes in participant anxiety disorder diagnosis according to DSM criteria. Using the ClinCalc LLC (2024) sample size calculation tool, the recruitment of 42 participants would be sufficient to detect a post-treatment between-group clinically meaningful change in anxiety disorder diagnosis with 80% power and alpha set to 0.05. This is based on the anticipated incidence of anxiety remission drawn from the metanalysis of Springer et al. (2018), which found that 55.8% of anxiety disorder diagnoses remitted after receiving CBT. For waitlist controls, anxiety disorder symptoms in participants in waitlist control fell below the clinical cut-score 15.4% of the time (Scott et al., 2022). Given CBT has not been examined in trials of LGBTQ+ participants with only internalising disorders (Van Der Pol-Harney & McAloon, 2018), an exact power analysis is unable to be determined and is thus an exploratory estimate. However, 95% confidence intervals will be reported with any effect estimates to determine the intervention's precision.

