**ANALYSIS PLAN**

To meet the study’s aim (i.e., to understand if the treatment is efficacious for reducing symptoms of anxiety disorders ), the following analyses will be conducted. The main analyses looking at treatment outcomes from the RCT will be carried out using conservative intention-to-treat principles and using mixed-linear models analyses to handle missing data. Mixed-models are a robust statistical approach for analysing longitudinal clinical trial data and these analyses will employ an appropriate covariance structure and maximum likelihood estimation, which provides unbiased estimates in the case of missing data, under the assumption that data is missing at random. These analyses account for the effect of missing data, thus additional participant recruitment to account for drop-out rates is not warranted. Using this dataset, other appropriate analyses arising from secondary papers will also be conducted. Participants have been informed in the PICF that other secondary data analyses will be conducted on the data that they provide during their participation in the research trial. This may include intersectional moderator analyses of treatment efficacy based on person-level stigma moderators from the minority stress model to inform further treatment adaption needs (Barrera & Castro, 2006; Meyer, 2003). Comparisons between the standard treatment and the LGBTQ-affirmative CBT protocol will be compared using benchmarking analyses (Minami et al., 2008).

To understand the treatment’s efficacy, clinically significant change will be measured using three methods. Diagnostic change will be assessed from pre- to post-treatment and at follow-up using the DIAMOND structured interview. Treatment response will be measured using the reliable change index (RCI) of Jacobson and Truax (1991) to understand which change on the OASIS is not attributable to measurement error, but rather is statistically reliable. Any increase in symptoms by the RCI magnitude of change will be defined as deterioration in this trial. Clinically significant change at post-treatment and to follow-up will be defined as a score below the cut score of 8 on the OASIS (Campbell-Sills et al., 2009).

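### Hypothesis 1 claims efficacy at three-month follow-up, where no untreated arm remains; only the post-treatment between-group contrast is randomised against no treatment and powered, and it should alone decide

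*Protocol*

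**What the plan says.** In the section on objectives, design and hypotheses, Hypothesis 1 states that standard CBT by video will "result in significant reductions in symptoms with a large between-group and within-group effect size at post-treatment and three-month follow-up". Hypothesis 2, in the same list, expects the LGBTQ-adapted treatment given to Group 2 to reduce symptoms to a similar degree.

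The Summary describes the trial as "comparing an immediate treatment group with a waitlist control group". The section on participant numbers and power says that "52 participants would be needed to detect a large, post-treatment, between-group effect size with alpha set to 0.05 and 80% power"; the Summary adds that the size was chosen "to detect a large effect (*d* = .80) with 80% power". The OASIS is the only primary measure.

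The Analysis Plan specifies intention-to-treat mixed models for the main analyses but does not say which contrast or time point decides efficacy. Its paragraph on clinically significant change begins: "Diagnostic change will be assessed from pre- to post-treatment and at follow-up using the DIAMOND structured interview".

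Table 1 assesses Group 1 at Week 0, mid-treatment, Week 9 and three-month follow-up. It assesses Group 2 at Week 0, at Week 9 before treatment, then mid-treatment, at Week 18 and at its own three-month follow-up.

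**The concern.** The primary objective is efficacy, and Hypothesis 1 is where efficacy is to be judged. It treats as equal evidence a randomised comparison with an untreated arm, a later comparison in which that arm has been treated, and two before-after changes with no control. These do not answer the same question.

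At follow-up the difficulty is structural. The hypothesis calls for a large between-group effect at a time when the design no longer supplies an untreated comparator. Either the between-group result there is read as CBT against no treatment, which it is not, or the claim rests on Group 1's change alone. Participants enter with a disorder of at least moderate severity, so some improvement without treatment is to be expected. A durable-efficacy statement could then be made on evidence that cannot separate treatment from time.

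**Working it through.** **1. Which contrast the sample size supports.** Inputs: d = 0.80, alpha 0.05, 80% power (Summary; section on participant numbers and power), equal groups. For a two-sample t-test with n per group, the noncentrality is d × √(n/2) on 2n − 2 degrees of freedom.

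- n = 25, two-sided: 0.8 × √12.5 = 2.83, power 0.791.
- n = 26, two-sided: 0.8 × √13 = 2.88, power 0.807.
- One-sided, 21 per group would be enough (power 0.817).

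The planned 52 is therefore reproduced as a two-sided, post-treatment, between-group test. The protocol does not state sidedness; the arithmetic points to two-sided. No figure in the protocol powers a within-group contrast or any contrast at follow-up.

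**2. Who is untreated, and when (Table 1).** Three months is taken as about 13 weeks.

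| Time | Group 1 | Group 2 | Between-group contrast estimates |
| --- | --- | --- | --- |
| Week 0 | untreated | untreated | baseline balance |
| Week 9 | post-treatment | untreated | standard CBT against waitlist |
| Week 18 | – | post-treatment | – |
| Week 9 + 13 = about 22 | three-month follow-up | treated, about 4 weeks past post-treatment | standard against adapted CBT |
| Week 18 + 13 = about 31 | – | three-month follow-up | – |

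Group 2 has no untreated assessment after Week 9. Matching the two follow-ups by time since treatment (Group 1 at about Week 22, Group 2 at about Week 31) still compares two treated groups. Setting Group 1 at Week 22 against Group 2 at Week 9 would confound treatment with time since randomisation. Parts of the protocol give the waitlist as eight weeks rather than nine; the conclusion is the same either way.

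**3. Hypothesis 1 beside Hypothesis 2.** At follow-up, a large between-group effect would mean that the two CBT versions differ greatly. Hypothesis 2 predicts that they are similar. Both predictions cannot hold there.

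**4. What uncontrolled change can show.** The protocol's own untreated figure is 15.4% of waitlist controls falling below the clinical cut-score: 26 × 0.154 = 4.0 participants. It gives no untreated change in SD units and no pre-post correlation, so the following is illustration under assumptions. For a paired t-test in Group 1 with no treatment effect, untreated change δ (in SD) and correlation r, the standardised change is δ / √(2(1 − r)) and the noncentrality is that value × √26.

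| Assumed δ (r = 0.5) | Chance of a significant reduction in Group 1 |
| --- | --- |
| 0.2 | 0.16 |
| 0.3 | 0.31 |
| 0.4 | 0.50 |
| 0.5 | 0.69 |

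At δ = 0.3, the chance runs from 0.24 (r = 0.3) to 0.48 (r = 0.7). With the 26.4% drop-out that the protocol cites, 26 × 0.736 gives about 19 participants, and the chance at δ = 0.3, r = 0.5 is 0.24. The randomised between-group test at Week 9 has a 0.025 chance of falsely favouring treatment, whatever the shared drift.

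**The case against.** The strongest reply is that the hypothesis joins its parts with the word and. Read as a joint condition, a null randomised comparison at post-treatment fails it, however much Group 1 improves. This is right. In a simulation of 40,000 trials with both arms improving equally by 0.2, 0.3 or 0.5 SD (26 per arm, r = 0.5), a significant within-group reduction together with a significant between-group benefit occurred in 1.0%, 1.6% and 2.1% of trials. A reader might infer that ordinary untreated improvement can be declared a treatment effect at post-treatment. That needs an either-or rule that the protocol nowhere states.

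It is also fair that the intended comparison can be found: the Summary gives the arms, the power section gives the post-treatment between-group effect, and the measures section gives the OASIS. The exact model contrast may belong in a statistical analysis plan. The three definitions of clinically significant change are participant-level and can be compared between arms.

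A reader might further infer that the trial fails unless the observed d reaches 0.8. The protocol does not say so: the large effect is a prediction and a planning value. It also calls its power analysis an exploratory estimate and promises 95% confidence intervals.

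None of this repairs the follow-up clause. The joint reading requires a large between-group effect at a time with no untreated group, and no analysis plan can supply one.

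**Conclusion.** The concern holds in a limited form. Of the four contrasts in Hypothesis 1, one is both randomised against an untreated arm and powered: between-group at post-treatment. At three-month follow-up the between-group effect cannot estimate CBT against no treatment, and a large one would contradict Hypothesis 2. Only uncontrolled change in Group 1 is left there as evidence for standard CBT.

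This rests on Table 1 and the wording of the two hypotheses, not on simulation. The rates for the within-group test depend on assumed drift and correlation and show only that such a test is weak evidence of efficacy. The documents do not support the wider reading that the protocol lacks any intended primary comparison, or that a null randomised result could satisfy Hypothesis 1 at post-treatment.

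**What to change.** In Hypothesis 1 and the Analysis Plan:

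- State that the Group 1 minus Group 2 difference in OASIS change from Week 0 to Week 9, from the intention-to-treat mixed model (two-sided 0.05, with 95% confidence interval), alone decides Hypothesis 1.
- Remove the between-group efficacy claim at three-month follow-up. Any comparison of the arms at that point belongs under Hypothesis 2, as one CBT version against the other.
- Report within-group effect sizes, and all follow-up effect sizes, as descriptive with confidence intervals.

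Table 1 already collects the OASIS in both groups at Week 0 and Week 9, so no further data are needed. The sample size stays at 52; the power of 0.807 is for d = 0.80 with all 26 per group observed. The cost is that within-group and follow-up results can no longer be presented as proof of efficacy.

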Cognitive behaviour therapy (CBT) is recommended as the gold-standard, first-line treatment for internalising disorders (American Psychological Association Presidential Task Force on Evidence-Based Practice, 2006; Australian Psychological Society, 2018; National Institute for Health and Care Excellence, 2011). CBT’s effectiveness has been shown across 106 meta-analyses, with a medium to large effect size for treating any internalising disorder (Hofmann et al., 2012). Comorbidity between internalising disorders is high (Kessler et al., 2011), and treatments have been developed to address multiple internalising disorders simultaneously. This is known as transdiagnostic treatment. The Unified Protocol (Ellard et al., 2010) is a well-researched type of transdiagnostic treatment that has been demonstrated to have large effect sizes for internalising disorders in the general population (Sakiris & Berle, 2019). Additionally, preliminary controlled trials have shown that an LGBTQ-adapted Unified Protocol for LGBTQ+ adults is also effective at reducing symptoms of internalising disorders (Ellard et al., 2010; Pachankis et al., 2015; Pachankis et al., 2020b). In two randomised control trials of LGBTQ+ adapted CBT, Pachankis et al. (2015) and Pachankis et al. (2020) found comparable effect sizes pre- to post-treatment for anxiety and related disorders and depressive symptoms as in trials of the Unified Protocol in the general population. It is important to understand if LGBTQ-adapted CBT is more effective than standard CBT, but to date, no clinical trials have directly compared the two treatments or measured standard CBT’s efficacy in LGBTQ+ people. This study will contribute to the emerging evidence of equivalence between the two treatments by understanding the preliminary efficacy of both interventions, and assessing feasibility to progress to a larger trial where both treatments are directly compared.

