**Table 1.**

*Administration Schedule for Outcome Measures*

|  | Screening | Group 1: Immediate Treatment | | | | Group 2: Control Group | | | | |
| --- | --- | --- | --- | --- | --- | --- | --- | --- | --- | --- |
|  | Both groups | Pre-(Week 0) | Mid- | Post-  (Week 9) | 3-month follow-up | Baseline  (Week 0) | Pre-  (Week 9) | Mid- | Post- (Week 18) | 3-month follow-up |
| **Screening Measures** |  |  |  |  |  |  |  |  |  |  |
| *Demographics* | + |  |  |  |  |  |  |  |  |  |
| *Risk questionnaire* | + |  |  |  |  |  |  |  |  |  |
| *DIAMOND Screener* | + |  |  |  |  |  |  |  |  |  |
| *DIAMOND Interview* | + |  |  | + | + |  | + |  | + | + |
| *C-SSRS* | + |  |  |  |  |  |  |  |  |  |
| **Primary Outcome Measures** | | | | | |  | | | | |
| *OASIS* |  | + | + | + | + | + | + | + | + | + |
| **Secondary Outcome** **Measures** | | | | | |  | | | | |
| *ODSIS* |  | + | + | + | + | + | + | + | + | + |
| *GAD-D* |  | + | + | + | + | + | + | + | + | + |
| *SAD-D* |  | + | + | + | + | + | + | + | + | + |
| *PD-D* |  | + | + | + | + | + | + | + | + | + |
| *AG-D* |  | + | + | + | + | + | + | + | + | + |
| *SP-D* |  | + | + | + | + | + | + | + | + | + |
| *SepAD-D* |  | + | + | + | + | + | + | + | + | + |
| *PHQ-9* | + | + | + | + | + | + | + | + | + | + |
| *HHRDS* |  | + | + | + | + | + | + | + | + | + |
| *RSQ-A* |  | + | + | + | + | + | + | + | + | + |
| *LGBIS* |  | + | + | + | + | + | + | + | + | + |
| *SOCS* |  | + | + | + | + | + | + | + | + | + |
| *CGI-S (Self-report)* | + | + | + | + | + | + | + | + | + | + |
| *CGI-I (Self-report)* |  |  | + | + | + |  |  | + | + | + |
| *CGI-S (Assessed)* | + | + | + | + | + | + | + | + | + | + |
| *CGI-I (Assessed)* |  |  | + | + | + |  |  | + | + | + |
| *SUQ* |  |  |  | + | + |  |  |  | + | + |
| *CEQ* |  | + |  |  |  |  | + |  |  |  |
| *AdQ* |  |  | + | + | + |  |  | + | + | + |
| Process Measures |  |  |  |  |  |  |  |  |  |  |
| *CSQ* |  |  | + | + |  |  |  | + | + |  |
| *AcQ* |  |  | + | + |  |  |  | + | + |  |
| *WAI-SF* |  |  | + | + |  |  |  | + | + |  |

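### Hypothesis 1 claims a between-group effect at three-month follow-up, when no untreated arm remains, and Hypothesis 2 claims similarity without a criterion

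*Protocol*

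**What the plan says.** In the protocol's section on objectives, design and hypotheses, Hypothesis 1 states that standard CBT will reduce symptoms "with a large between-group and within-group effect size at post-treatment and three-month follow-up". Hypothesis 2 states that "LGBTQ-adapted CBT will result in a similar degree of symptom reduction when compared to standard CBT".

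Group 1 receives standard CBT at once. Group 2 waits and then receives the adapted version. Table 1 places Group 1's post-treatment visit and Group 2's pre-treatment visit both at week 9. Group 2's later columns (mid-treatment, then "Post- (Week 18) | 3-month follow-up") all fall after its treatment has begun. Under Questionnaire Administration, follow-up is three months after each participant's own treatment.

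The power section covers only a "large, post-treatment, between-group effect size with alpha set to 0.05 and 80% power". The Summary gives "A total sample of 52 participants, with 26 participants in each group".

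For adapted versus standard CBT, the Analysis Plan says: "Comparisons between the standard treatment and the LGBTQ-affirmative CBT protocol will be compared using benchmarking analyses". No margin or definition of similarity is given. The Background says: "This study will contribute to the emerging evidence of equivalence between the two treatments". The same sentence leaves direct comparison to a larger trial.

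**The concern.** A between-group effect attributed to CBT needs a group without CBT at the same time. The design has one at week 9 and none later. As written, one part of the main efficacy hypothesis has no comparator. A small follow-up difference between two treated arms could be taken as loss of effect or as support for equivalence, and would show neither.

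Hypothesis 2 has a related difficulty. With no criterion, any observed difference could be called similar or not similar, and the sample size was chosen for another question. Group 2 also enters treatment after nine weeks of natural course and after any loss during the wait, so its pre-to-post change is not like-for-like with Group 1's.

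**Working it through.** **1. The plan's own sample size.** The Summary specifies "samples of 26 for each group, to detect a large effect (*d* = .80) with 80% power". A two-sided two-sample t-test at alpha 0.05 (sidedness is not stated, but two-sided reproduces the figure) has df = 2n − 2 and noncentrality d·√(n/2).
- n = 25 per arm: power 79.1%.
- n = 26 per arm: noncentrality 0.80 × √13 = 2.88, power 80.7%.

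The total of 52 is reproduced. It applies to the week 9 contrast only.

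**2. Which contrasts exist.** Three months is taken as 12 to 13 weeks.

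| Time from week 0 | Group 1 | Group 2 |
|---|---|---|
| Week 9 | Post-treatment | Untreated, pre-treatment |
| Week 18 | No visit | Post-treatment |
| Week 21–22 (9 + 12 to 13) | Follow-up | No visit; treatment already finished |
| Week 30–31 (18 + 12 to 13) | No visit | Follow-up |

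Matching by visit label compares standard with adapted CBT. Matching by elapsed time finds no Group 2 assessment near Group 1's follow-up, and Group 2 has been treated by then in any case. Only week 9 gives treated versus untreated. The Summary and the Treatment section also mention an eight-week wait, which should be reconciled with the nine weeks stated elsewhere. The result is the same under either.

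**3. Follow-up if Hypothesis 2 is true.** With 26 per arm, a between-arm test has a rejection probability of 5% at a true difference of 0 and 11% at a true difference of 0.2 SD. A difference of 0.8 SD there would mean that the two treatments are not similar. At week 9 there is no conflict, because Hypothesis 1 then compares CBT with waiting.

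**4. Precision for Hypothesis 2.** In SD units of the outcome, half-width = t(0.975, 2n − 2) × √(2/n).
- 26 per arm: 2.009 × 0.277 = 0.56 SD.
- 18 per arm (the protocol's 70% retention threshold, 0.70 × 26 = 18.2): 2.032 × 0.333 = 0.68 SD.
- 26 per arm with baseline adjustment, multiplying by √(1 − r²): 0.48 SD at r = 0.5 and 0.40 SD at r = 0.7. Both values of r are assumptions.

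**5. Margin at which similarity could be shown.** For two one-sided tests at 0.05 each, a true difference of 0 and 80% power, margin = (1.645 + 1.282) × √(2/n).
- 26 per arm, unadjusted: 2.927 × 0.277 = 0.81 SD.
- 26 per arm, adjusted: 0.70 SD at r = 0.5 and 0.58 SD at r = 0.7.
- 18 per arm, unadjusted: 0.98 SD.

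The protocol sets no margin, so the power of this test (simulated, 26 per arm, unadjusted) is shown over a range.

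| Assumed margin (SD) | Power |
|---|---|
| 0.3 | 0% |
| 0.4 | 0.5% |
| 0.5 | 12% |
| 0.6 | 38% |
| 0.8 | 77% |

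At 0.5 SD, power is 32% with r = 0.5, 60% with r = 0.7, and 1.6% with 18 per arm unadjusted.

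**6. The wait.** The protocol's power section expects 15.4% of waitlisted participants to fall below the clinical cut-score, about 4 of 26 (0.154 × 26 = 4.0). Its feasibility threshold for retention after the wait is 80%, or about 21 of 26 (0.80 × 26 = 20.8). Either can shift Group 2's starting level and composition before its first session.

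**The case against.** The strongest reply is that Hypothesis 1 compresses two effect types and two time points into one clause, and may mean between-group at post-treatment and within-group at follow-up. The power section supports that reading, since it covers post-treatment only. No analysis text specifies a between-arm test at follow-up, and Table 1 already aligns the two week 9 visits. Three of the four elements of Hypothesis 1 remain testable. The coding of time may sit in a statistical analysis plan that is not shown. All of this is fair, but the hypothesis itself is a protocol statement, its literal reading includes follow-up, and nothing elsewhere corrects it.

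On Hypothesis 2, the protocol plans benchmarking and no equivalence test. It calls its power estimate exploratory, promises 95% confidence intervals, and says in the Treatment section that research is too sparse to conclude equivalence. That stands. The power figures above describe what the sample could support; they do not describe a planned test that fails.

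Stronger readings that the documents do not support:
- That the two hypotheses contradict each other throughout. They conflict only at follow-up, and only if the between-group claim applies there.
- That similarity cannot be shown at all. This depends on a margin the protocol does not set, and improves with baseline adjustment.
- That one arm will serve as an error-free benchmark for the other, with an inflated error rate. No text says its sampling error will be ignored.
- That the sample size is miscalculated. It reproduces.

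**Conclusion.** The point holds in this limited form. The between-group claim at three-month follow-up cannot be tested as an effect of CBT, because no untreated comparator exists after week 9. This follows from the schedule alone and needs no numerical assumption. The week 9 contrast and its sample size are sound.

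For Hypothesis 2, the trial can estimate the adapted-versus-standard difference to about ±0.56 SD unadjusted, narrower with baseline adjustment and wider with dropout. It can support similarity only within a wide margin, about 0.8 SD for 80% power unadjusted. These figures assume 26 analysed per arm, equal SDs and a true difference of zero. The margins and correlations are illustrative. The estimate remains confounded with the wait whatever the sample size.

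**What to change.** - **Hypothesis 1:** restrict the between-group claim to OASIS at week 9 from randomisation, Group 1 post-treatment against Group 2 pre-treatment. State that Group 2 data collected after its treatment starts do not enter that contrast. Make the three-month claim within-group only, as maintenance of change.
- **Hypothesis 2:** reword as estimation. Report the adapted-versus-standard difference in pre-to-post OASIS change, with Group 2's pre value taken at week 9, and a 95% confidence interval that carries the sampling error of both arms. Label the comparison as not like-for-like because of the wait, and draw no similarity or equivalence conclusion. Align the Background sentence on equivalence with this.

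The cost is wording in the hypotheses, the Background and the Analysis Plan. No new data, visits or participants are needed. The downside is that the follow-up between-group claim and the similarity claim are given up.
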